#### Exclusion criteria

People with mild (GDS 3) or very severe dementia (GDS >6) and those who have severe loss of hearing and/or vision will be excluded from the study.

#### Blinding (masking)

In order to prevent bias and to ensure that the intervention conditions are met (and not mixed up), the care providers from the 14 nursing home wards involved in the study will be informed of which persons in the ward are assigned to the experimental or control groups. Only (in)formal carers of the residents in the experimental group however, will be informed in detail about the Photo-Activity intervention during the study. Professional carers who are not the primary care provider (thus not providing either the experimental or control activity) will be invited to participate as Independent Assessors to fill in the outcome measures. They will not be informed on which residents will be offered the experimental or control intervention. Due to the small teams working in each ward, especially those in small-scale living arrangements, it might not always be possible to blind the Independent Assessors from knowing which intervention sessions the residents are assigned to. However, because the Independent Assessors are not present during the experimental or control sessions or trainings, and they do not provide the interventions themselves, the risk of bias is limited.

## Interventions and procedures

### Photo-activity intervention (experimental group)

#### Training

The (in)formal carers assigned to the experimental group, will be informed about the background, method, and application of the Photo-Activity intervention app, by a member of the research team. A short video from the artist [name], who originally developed the intervention, will also be shown.

A 75-minute training session on how to hold conversations around the artistic photographs with the residents will be given by a senior member of the research team. The training will include basic interview techniques that foster rapport, like asking open questions instead of closed ones, reflective listening and summarizing. The (in)formal carers in the experimental group will also be trained to use ‘person-enhancing communication strategies’ such as offering comfort (in the form of warmth, security, and conversing in a relaxed pace), supporting identity (through respect and acceptance), and offering opportunities for attachment (recognition, affirmation, sincerity) as opposed to ‘predatory communication strategies’ such as withholding comfort (being intimidating, abstaining, speeding up the conversation), not supporting identity (childish, labelling, belittling), and not allowing oneself to be attached (accusing, deceiving, not acknowledging) [4]. Finally, they will also be instructed to avoid questions that would seem to ‘test’ the residents about their interests or to recognize certain photos; rather any response from the residents is acceptable i.e. there is no right or wrong. The (in)formal carers are informed that all the information on ‘person enhancing communication strategies’ can also be found in the Photo-Activity app.

(In)formal carers participating in the training will be given their own unique code to access the app, besides a unique code they receive for each resident to which they provide the Photo-Activity. They will be invited to spend time on the app in order to familiarize themselves with the functions, i.e.: selecting a series of photos based on the interests profile of the resident with dementia, saving photos in the ‘conversation basket’, showing the photo series in full screen presentation mode, selecting favorite photos, or taking notes about photos that elicited the most/least reactions, or were more/less appreciated by the resident.

#### Intervention

The resident and their trained (in)formal carer will meet for 30 minute sessions, two times a week, for 4 weeks to talk about artistic photos on the app which they will view together using a tablet computer. The photos will be selected by the (in)formal carer delivering the Photo-Activity, based on a personal interest profile in which the interests of the resident, as inventoried in a pre-interview with them and/or their (in)formal carers, are described. Once 15-20 photos reflecting the interests of the resident are chosen from the app, the (in)formal carer spends half an hour with the resident in a quiet place, offering them something to drink while looking through the photos on the tablet. There is no set time for viewing each photo, and there is no requirement that the whole set of 15-20 photos should be viewed. They can spend as much time as they like viewing one photo for as long as reactions or stories are evoked from the resident.

### General conversation activity (control group)

#### Training

The (in)formal carers in the control group, will receive a short 45-minute training by a senior member of the research team to inform them about what the research project entails. They will be instructed to hold general conversations on random topics with the resident. They can freely choose the topic or address the topics that the resident brings up. No photos will be shown during the general conversation activity. The (in)formal carers in the control group will also be trained in engaging the resident in conversation using basic interview techniques for rapport building (open and closed questions, reflective listening, summarizing). They do not receive training in person-enhancing communication strategies.

#### Intervention

For the control group, the (in)formal carers will also have 30 minute sessions with the resident, two times a week for four weeks, in a quiet place within the nursing home. They will offer the resident something to drink, and spend the 30 minutes having a general conversation.

### Procedure for student observers

Research interns and nursing students will receive a 60-minute training session from a member of the research team in observing the behaviour of the resident during the experimental and control conditions, using the INTERACT [56]. The INTERACT scale has 22 items with 5 answer options ranging from ‘Not at all’ to ‘Nearly all the time’, and is used to rate the mood, speech, relation to another person or to the environment, need for prompting, and stimulation level of a person with dementia during a therapy session [57], as well as any negative interactions like reluctance, complaining or aggression [58]. The students will also rehearse how they can give constructive feedback to the (in)formal carers carrying out the intervention regarding communication styles and techniques when communicating with the resident.

## Outcome measures and products

For Phase I of the study (Design and development of the Photo-Activity intervention app), data will be collected in writing from user feedback meeting rounds and user testing of prototypes. Feedback, comments, and insights from the user groups ((in)formal carers, PWD and researchers) will be collected per meeting and reported anonymously. At the end of the development phase, the System Usability Scale (SUS), a short 10-item questionnaire that assesses perceived usability [59], will be given to the (in)formal carers- who were involved in the app development to evaluate its usefulness and user-friendliness. Observations of the persons with dementia themselves during the user tests will be conducted by trained student observers with the INTERACT observation scale [56] (see Phase II outcomes).

Data from Phase II (Implementation and assessment of impact of the Photo-Activity intervention) will be partly quantitative and partly qualitative. Data on background characteristics based on The Older Persons and Informal Caregivers Survey Minimum Data Set or TOPICS-MDS [60]; -such as age, gender, ethnicity, civil/marital status, education level, children, hours of paid or volunteer work, work function will be collected from the PWD and their (in)formal carers. In addition, the following primary and secondary outcomes will also be collected:

### Quantitative measures

#### Primary outcomes

For the residents, positive emotions and social interaction with their (in)formal caregiver during the activity session are assessed by trained students with the INTERACT observation scale [56] during the first and last intervention session.

Quality of life is evaluated by formal carers who are assigned the role of Independent Assessors, with the QUALIDEM [61] based on their observations of the behaviour of the resident in the previous week at T0, T1, and T2. These formal carers are trained in the use of the instrument by a member of the research team. The QUALIDEM was developed specifically to measure quality of life of residents with dementia living in nursing homes, as rated by the formal carers. It is made up of 37 items that describe behaviour that can be observed by the carer. Carers can choose from the answer options of ‘never, seldom, sometimes, and often [62]. The QUALIDEM has been found to have sufficient reliability and validity, and is an easy questionnaire to administer [61, 62].

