### Study setting and participants

The study will be conducted in 14 nursing home wards that are part of 2 large care organizations in the Netherlands (in the Amsterdam and Haarlem region). PWD in these participating nursing home wards who meet the inclusion and exclusion criteria (regardless of gender, age, socioeconomic status, and ethnicity), along with their legal guardians, will receive a written invitation from the nursing home with a consent form for participation and information about the study.

Based on the pilot study with the Photo-Activity, in which large positive effect sizes were found for social interaction (d= 0.86) and reduced negative behaviour (*d*=0.85) using the INTERACT scale [55] during the intervention [35], a power-analysis (power 0.80, α=0.05, *d*=0.8) and expected 10% dropout in 6 weeks, for this explorative study 45 people with dementia are needed per group (total of 90) to find statistically significant large effects. The researchers will promote the project in the care organizations and work with the research coordinators, ward managers and team leaders in order to meet the required recruitment target.

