**Primary outcomes**				
Student observer/ PWD		INTERACT Observation Scale (Session 1 and 8)		
Independent assessor	QUALIDEM		QUALIDEM	QUALIDEM

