## Analysis

### Quantitative data

Analysis for quantitative data will be done using SPSS for Windows. Participant characteristics are analyzed with descriptive statistics and differences are tested with parametric or non-parametric tests dependent on type of data. Multilevel analysis (MLA) is performed to investigate whether the averages on continuous outcome measures at T1 and T2 differ between experimental and control groups. Baseline measurements (T0), severity of dementia and potential confounders are included in the analyses as covariates. The MLA takes into account the clustering of people with dementia and caregivers within nursing wards. The same procedure is used for dichotomous data, but the analyses are then performed with General Estimations Equations. Both intention-to-treat and ‘per protocol’ analyses will be done.

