### Ancillary and post-trial care

If the participating nursing homes view the Photo-Activity intervention as a positive addition to their services, then the (in)formal carers will be given free access to the web-app after the study period is completed, to avoid data of active and non-active study participants being collected in Google Analytics. However, for residents in the Photo-Activity, they will still be able to use the web-app after follow-up at T2, because the researchers will have a record of the Photo-Activity session times that they can match to Google Analytics.

Training on the use of the web-app and the Photo-Activity intervention will also be made available to nursing staff of the participating nursing homes who are interested in the Photo-Activity, but provided the control intervention or were not involved in providing the interventions. If the intervention proves to be effective, an implementation toolkit will be developed to promote further implementation in the participating nursing homes, as well as dissemination to other nursing homes across the country.

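### Three primary outcomes are named without a ranking, while the sample size is planned on one α of 0.05 and one effect size, so the error rate behind a claim of effectiveness is not fixed

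*Protocol article*

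**What the plan says.** The section Primary outcomes of the protocol article names three constructs:

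- Positive emotions and social interaction, both from INTERACT: "positive emotions and social interaction with their (in)formal caregiver during the activity session are assessed by trained students". Table 1 gives the occasions as "INTERACT Observation Scale (Session 1 and 8".
- Quality of life on the QUALIDEM, rated by independent assessors "based on their observations of the behaviour of the resident in the previous week at T0, T1, and T2".

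No outcome is put first and no time point is made decisive.

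Study setting and participants gives "a power-analysis (power 0.80, α=0.05, *d*=0.8) and expected 10% dropout in 6 weeks", and concludes that "for this explorative study 45 people with dementia are needed per group (total of 90) to find statistically significant large effects". The pilot values cited in support are both from INTERACT: 0.86 for social interaction and 0.85 for reduced negative behaviour. Negative behaviour is not one of the named primary outcomes. No pilot value is given for positive emotions or for quality of life.

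The Analysis section plans multilevel models "to investigate whether the averages on continuous outcome measures at T1 and T2 differ between experimental and control groups", with baseline as a covariate. It runs both intention-to-treat and per-protocol analyses.

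Ancillary and post-trial care says: "If the intervention proves to be effective, an implementation toolkit will be developed to promote further implementation". Objectives words the condition differently: the toolkit follows if the intervention proves feasible and is evaluated positively. The abstract and Methods/Design base it on the process evaluation.

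**The concern.** A power calculation with one α and one d describes one comparison. Here three outcomes share primary status and each has two observations after randomisation. A reader of the results could not tell which finding the 5% error rate belongs to. If one outcome or time point is significant and the others are not, the article gives no rule for whether the trial has succeeded.

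This matters because the article does speak of the intervention proving effective, although it calls the study explorative. Without a rule fixed in advance, the choice of which primary result supports that statement can be made after the data are seen. Which outcome is primary, and which one the sample size serves, belongs in the protocol. It is not a detail that is usually left to the analysis plan.

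**Working it through.** **Inputs.** From Study setting and participants: α = 0.05 (taken as two-sided; the article does not say), power 0.80, d = 0.8, dropout 10%, 45 per group. From Primary outcomes and Table 1: three constructs. INTERACT is taken at sessions 1 and 8. QUALIDEM is taken at T0, T1 and T2, of which two are after baseline. Correlations between tests are not given and are assumed below.

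**The plan's own figure.** Per group, n = 2(1.96 + 0.84)²/0.8² = 24.5, so 25 (26 with the t-test). Dividing by 0.9 gives 28 (29), not 45. The stated 45 leaves about 40 evaluable per group (45 × 0.9 = 40.5). The article does not explain the difference. It could be a design effect of about 40/26 = 1.54 to 40/25 = 1.6, but none is mentioned. This mismatch is a separate matter. It is relevant here only because the apparent margin may already be needed for clustering.

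**Chance of at least one p < 0.05 when there is no effect.** For independent tests this is 1 − 0.95^k:

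- k = 3 (one test per primary outcome): 1 − 0.857 = 14.3%.
- k = 6 (two occasions per outcome): 1 − 0.735 = 26.5%.

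Simulated two-sided normal tests with an assumed equal correlation give:

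| Assumed correlation | 3 tests | 6 tests |
|---|---|---|
| 0.3 | 13.6% | 24.1% |
| 0.5 | 12.6% | 20.7% |
| 0.7 | 10.9% | 16.4% |
| 0.9 | 8.4% | 10.8% |

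**Dependence on the rule.** These figures need a rule that any one significant result counts. If all three outcomes had to be significant at 0.05, the error would not exceed 5%.

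**Can the planned sample carry an adjustment?** The t-test power at d = 0.8 with 40 evaluable per group is shown below. The last column divides 40 by an assumed design effect of 1.5, giving an effective 26.7 per group.

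| α | No clustering | Assumed design effect 1.5 |
|---|---|---|
| 0.05 (one primary) | 94% | 82% |
| 0.05/3 | 87% | 67% |
| 0.05/6 | 80% | 57% |

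The row for α = 0.05/3 is the first Holm step with three outcomes. Applying d = 0.8 to positive emotions or QUALIDEM is a further assumption, because the article gives no effect size for either.

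**The case against.** The strongest reply is that the study calls itself explorative, that multiplicity rules commonly sit in an analysis plan, and that the article claims no family-wise error control. This stands as far as it goes: the absence of an adjustment method is not in itself a fault here. It does not cover the choice of primary outcome. The article makes that choice, and leaves three outcomes level against a calculation for one.

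Three stronger readings are tempting, and the article does not support them.

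- A reader might infer that the effectiveness claim has a false-positive rate of 14% to 26%. Those are the values for independent tests under an any-one-counts rule that is stated nowhere. Two of the constructs come from the same scale, observer and sessions, and repeated measures on one resident are correlated, so lower values are likely.
- A reader might infer that six tests are planned. The T1 and T2 comparison does not fit INTERACT, which has only session 1 and session 8 values, and a multilevel model could give one group effect per outcome. Three primary outcomes are certain; six tests are not.
- A reader might infer that a chance finding would by itself trigger national rollout. The abstract, Objectives and Methods/Design tie the toolkit to feasibility, positive evaluation and the process evaluation. Only Ancillary and post-trial care ties it to effectiveness, and no section ties it to a p-value.

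It might also be said that the 90 residents already pay for an adjustment. That holds only if ward clustering is ignored, and the Analysis section itself says that clustering must be taken into account.

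**Conclusion.** The point holds in a limited form. The article fixes three unranked primary outcomes against one α and one d, and only social interaction among them has a stated pilot effect size. If any single significant primary result were taken as showing effectiveness, the false-positive rate would be up to about 14% for three tests, or 11% to 14% at assumed correlations of 0.3 to 0.7. It would be up to about 26% if both occasions of each outcome were tested separately, or 16% to 24% at the same correlations. Even at an assumed correlation of 0.9 both figures exceed 5%. The actual rate cannot be derived from the text, because neither the success rule nor the number of tests is stated.

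This should be corrected before analysis. It does not invalidate the design.

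**What to change.** Choose one of the following and state it in Primary outcomes:

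1. Name INTERACT social interaction at the last session (session 8) as the primary outcome, and make positive emotions and QUALIDEM at T1 secondary.
2. Keep all three as primary, each at one fixed time point, with Holm's procedure across them.
3. Present all results as exploratory and make no claim of effectiveness.

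Then define, in Ancillary and post-trial care, what proving effective means under that choice. Reconcile that sentence with the feasibility and process-evaluation conditions in Objectives and Methods/Design.

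The cost is a few sentences. Option 1 keeps α at 0.05 for the primary outcome and adds no residents; the price is that the other two outcomes lose primary status. Option 2 sets a stricter threshold. At d = 0.8 with 40 evaluable per group, power at α = 0.05/3 is about 87% without clustering and about 67% at an assumed design effect of 1.5. Option 1 is therefore the cheaper of the two.

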#### Secondary outcomes

For the residents, their mood will be assessed with the one item self-reported five-point visual analogue scale known as the Smiley Face Expression Scale (SFAS) [63] during the first and last intervention week (2 sessions per week). The faces in the SFAS corresponds to moods that reflect a range from ‘very unhappy’ to ‘very happy’, and the SFAS has been previously used in other studies to evaluate mood of PWD [63–65]. There seems to be no previous studies that have established the validity of the SFAS, but it was found to be an effective measurement of PWD in an art museum intervention [63], and in general, similar visual analogue scales that measure mood of PWD have shown good validity [64, 66].

The Independent Assessor’s assessment of mood and behavioural symptoms of the resident will be evaluated with the brief Neuropsychiatric Inventory (NPI-Q), for assessing psychopathology in dementia [67] at T0, T1 and T2. The NPI-Q was found to be a reliable and valid assessment of neuropsychiatric symptoms, covering 12 symptom domains [67, 68]. The carer rates the frequency (ranging from 1-4) and severity (ranging from 1-3) of symptoms, and also rates their level of distress for every symptom present, from 0 (not distressing at all) to 5 (extremely distressing). The care provider answering the NPI-Q is the same one who fills out the QUALIDEM [61].

Person-centered attitude of the (in)formal care providers involved in the experimental or control conditions with the resident is examined with the Approaches to Dementia Questionnaire (ADQ) [69], which has 19 statements about resident and how they are cared for, with a five-point Likert scale ranging from ‘strongly agree’ to ‘strongly disagree’. The ADQ has been found to have good validity and reliability [69–71].

Empathy will be measured using the Interpersonal Reactivity Index (IRI), which has 28 items measuring global empathy, with subscales on perspective taking, fantasy, empathic concern, and personal distress. It can be answered on a 5-point Likert scale ranging from ‘does not describe me well’ to ‘describes me very well’ [72]. The IRI has been found to be valid and reliable [73].

Both the ADQ [69] and the IRI [72] will be completed on T0 and T1 by the (in)formal care providers in the experimental and control groups. (In)formal carers in the experimental condition will additionally be asked to complete the System Usability Scale (SUS) [59] at T1. SUS is a well-known brief scale for measuring perceived usability, and has been found to have excellent reliability and concurrent validity [74].

For the informal carers, their feelings of competence in dealing with the PWD is evaluated using the Short Sense of Competence Questionnaire (SSCQ) [75] during T0, T1 and T2. The SSCQ, which assesses issues experienced by the informal carer, has 7 items that can be answered on a 5-point Likert scale ranging from ‘completely agree’ to ‘completely disagree’. It has satisfactory validity and reliability [76].

For the duration of Phase II, intervention compliance will be monitored by asking (in)formal carers to record the dates, times, and duration of their sessions with the residents in both experimental and control group, along with life events that may impact the residents or (in)formal carers (such as illness, hospitalization, or death of loved ones) and other reasons for drop-out.

A summary of outcome measures and timeframe for completion is shown on Table 1.

**Table 1 Tab1:** Quantitative outcome measures and timeframe for completion

	T0	During Intervention Period	T1	T2
